## Methods/design

### Study settings

This clinical trial will be conducted at the Liaoning Cancer Hospital Medical Center (a tertiary care center) in China. This is a prospective study enrolling 102 patients. We aim to investigate the safety and efficacy of radiotherapy in patients with brain metastases caused by SCLC using the TOMO treatment device. Using the random number table method, a random number sequence will be generated, and patients will be assigned to the experimental and control groups in a 1:1 ratio. The experimental group will use TOMO, while the control group will use three-dimensional conformal radiotherapy (conventional 3D-CRT)/intensity-modulated radiation therapy tomotherapy (IMRT). This study will not use blinding of trial participants since the treatment procedure clearly distinguishes between the trial and control groups.

The trial sponsors are the Shenyang Major Scientific Research Projects [No. 191124090] and the Cancer Research Program of National Cancer Center [NCC2017A08]. This is version 1.0 of the protocol as of January 1, 2021. Recruitment for this clinical trial began on April 1, 2021 and will end on March 31, 2024.

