#### Overall survival

Overall survival (OS) refers to the number of months between the radiotherapy procedure and the time of death or last follow-up. For patients who are lost to follow-up prior to death, the time of the last follow-up visit is usually calculated as the time of death.

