### Data analysis

After the last patient completes the follow-up study, the committee will assess the occurrence of the primary and secondary endpoints. Treatments in participant timeline are all routine medical orders, and patients will follow the medical advice. If there is any failure to review on time, a phone call will be reminded. If the patient fails to complete the relevant examination, evaluation or follow-up within the agreed time, or cannot suspend the study, part of the clinical trial of the patient will be suspended. The data of these patients will be marked on the record and not entered in the final curative effect analysis system. The fixed staff is responsible for the input of data, coded into groups 1 and 2 according to their treatment plans, and set a password for the database to protect the privacy of patients’ data. Data quality is controlled by the Data Quality Supervision Committee.

Data will be organized and analyzed using the SPSS 25.0 software, and *P* < 0.05 will be considered significant in all statistical tests. iPFS and OS will be calculated using the Kaplan-Meier method. Assessment of neurological function will be scored using the EDSS assessment scale, and QoL will be scored using the FACT-G. The chi-squared test will be used in combination with propensity matching analysis to minimize differences due to smoking, sex, weight loss, geographic factors, economic status, and education level and to avoid baseline effects to the greatest extent possible. Definition of analysis population relating to protocol non-adherence is that the patients who do not follow. In addition, we use the multiple imputation method to handle missing data.

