## Dissemination

### Data monitoring

The Data Monitoring Committee (DMC) is composed of all the authors, with [name] as the team leader, responsible for testing the accuracy and authenticity of data and reviewing whether the operation of obtaining data is standardized. If the patient fails to complete the relevant examination, evaluation, or follow-up within the agreed time or cannot suspend the study, part of the clinical trial of the patient will be suspended.

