### Suspension of clinical trials standards

If a patient fails to suspend the clinical trial to complete the relevant tests, or to complete the follow-up assessment within the agreed upon time frame, in the following circumstances, or if the study if not suspended, that portion of the patient’s specific clinical trial will be suspended.

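### The protocol removes randomised patients from the efficacy analysis if they miss an examination, evaluation or follow-up, a post-randomisation exclusion plausibly related to progression or decline

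*Protocol article*

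**What the plan says.** The Data analysis section first provides a telephone reminder for patients who do not attend on time. It then sets a trigger: "If the patient fails to complete the relevant examination, evaluation or follow-up within the agreed time". Such a patient has part of the trial suspended, and the next sentence gives the consequence for the analysis: "The data of these patients will be marked on the record and not entered in the final curative effect analysis system".

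The trigger appears twice more. Data monitoring has "within the agreed time or cannot suspend the study, part of the clinical trial of the patient will be suspended", and Suspension of clinical trials standards has "or to complete the follow-up assessment within the agreed upon time frame".

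Three other statements bear on the same patients:

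- The sentence meant to define the analysis population breaks off: "Definition of analysis population relating to protocol non-adherence is that the patients who do not follow".
- The Data analysis section closes with "In addition, we use the multiple imputation method to handle missing data".
- For patients lost before death, the Overall survival section says that "the time of the last follow-up visit is usually calculated as the time of death".

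No section states that all randomised patients are analysed as assigned.

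**The concern.** The trigger occurs after randomisation and concerns the visits at which the endpoint is measured. Under Post TOMO follow-up, the reviews include the brain MRI used to look for recurrence, and the primary outcome is time to first evidence of progression. Patients whose brain disease progresses, or whose neurological state declines, are plausibly the ones who miss visits. Removing them leaves two groups that are no longer the groups randomised, for iPFS, overall survival and neurological function alike.

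The rule can also discard information already collected. Unless it is limited in some way the text does not state, a patient with a recorded progression who later misses a visit leaves the efficacy analysis together with that event.

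Study settings says "This study will not use blinding of trial participants". Attendance could therefore differ between arms, and a difference in who is excluded would bias the comparison. If exclusion is the same in both arms, the cost to the comparison is mainly power, although each arm's own iPFS could still look too favourable if progressing patients are the ones removed.

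**Working it through.** **1. The statements side by side**

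| Section | What happens to a patient who misses assessments |
|---|---|
| Data analysis, exclusion sentence | Data kept out of the efficacy analysis |
| Data analysis, imputation sentence | Missing data are imputed |
| Data analysis, Kaplan-Meier | Can use the patient up to the last assessment by censoring |
| Overall survival | Patient stays in, with the last visit usually taken as death |

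Imputation can still fill gaps in patients who are retained, so it is not wholly void. For the excluded patients it has nothing to act on. For a patient lost before death, the exclusion sentence and the Overall survival section cannot both be followed.

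**2. The protocol's sample size**

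Inputs from Sample size: σ = 1.8 months, δ = 1 month, z values 1.96 and 0.842.

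n per arm = 2 × [(1.96 + 0.842) × 1.8 / 1]² = 2 × 5.0436² = 50.88, rounded to 51. The stated figure reproduces. Nothing is added for attrition.

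**3. Power if patients are excluded**

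Power = Φ(√(n/2) × δ/σ − 1.96). The exclusion rates are assumptions, since the protocol gives none.

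| Assumed share excluded | n per arm left | √(n/2)/1.8 | less 1.96 | Power |
|---|---|---|---|---|
| 0% | 51 | 2.805 | 0.845 | 80.1% |
| 5% | 48.45 | 2.734 | 0.774 | 78.1% |
| 10% | 45.9 | 2.661 | 0.701 | 75.8% |
| 20% | 40.8 | 2.509 | 0.549 | 70.9% |
| 30% | 35.7 | 2.347 | 0.387 | 65.1% |

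This is the protocol's comparison-of-means formula. iPFS is to be analysed by Kaplan-Meier, where power depends on events, so the table is only a rough guide.

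**4. When the comparison is biased**

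Illustrative simulation with no true difference: exponential iPFS with median 8 months in both arms, 24 months of follow-up, 51 per arm, log-rank test, 4,000 trials.

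- Equal exclusion (20% of those progressing before month 6 and 5% of the others, in both arms): hazard ratio about 1.00, two-sided false positives about 5%.
- Unequal exclusion (30% v 10% of those progressing before month 6, 5% of the others): hazard ratio about 1.09 in favour of the arm losing more early progressors, false positives about 6.9%.

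Bias between the arms therefore needs exclusion that differs by arm.

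**5. What remains if everyone is analysed**

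A second illustration, again with no true difference: median iPFS 6 months, median 3 months from progression to death, reviews at 2, 4, 6, 12, 18 and 24 months, and 2% of reviews missed before progression. After progression, 5% are missed in one arm and 20% in the other. Progression is dated at the review that detects it. Two codings of this model gave these two-sided false-positive rates:

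| Handling | False positives |
|---|---|
| Any miss excludes the patient | 8.5% to 8.9% |
| Only misses up to detection of progression exclude | 5.9% to 6.4% |
| All analysed, censored at last MRI if no progression recorded | 6.7% to 7.5% |

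Analysing everyone reduces the distortion only in part on the wide reading and does not reduce it on the narrow one. Missed reviews still delay or lose the detection of progression.

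**The case against.** **The scope is uncertain.** The trigger sentence is garbled, only part of the patient's trial is suspended, and the text does not say whether a miss after recorded progression counts. The imputation plan and the survival rule suggest that dropping a whole patient for one late visit may not be intended. This stands as a limit on size. It does not remove the point, because the exclusion sentence refers to the data of these patients without qualification and no other section brings them back. Nor is this a detail left to an analysis plan: it is a rule stated outright.

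**The bias figures rest on invented inputs.** This also stands. The protocol gives no missed-visit rate, no median iPFS and no expected difference in attendance. Both arms receive whole brain radiotherapy with a boost and share one review schedule, and patients are telephoned after a missed review. A reader might infer that the rule would create a false iPFS gain as large as the 5–8% hypothesised in Background. With 5% v 20% of reviews missed after progression, and any miss excluding the patient, a model based on true progression times does give a spurious gain of about 8–13% in median iPFS. That needs a fourfold difference in attendance and the widest reading, and the documents support neither.

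**The fix does not cure unequal attendance.** This stands as well, as step 5 shows. A reader might also infer that analysing everyone restores exactly 80% power. It does not, since censoring loses events too. The case for the change is that it keeps the randomised groups and the recorded data.

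**Conclusion.** The point holds. As written, the protocol removes randomised patients from the efficacy analysis because of an event during follow-up that is plausibly related to the outcome, and it contradicts its own handling of missing data and of patients lost to follow-up. The existence of the rule is certain. The link to progression is a reasonable inference, and the scope is unclear.

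Neither the size nor the direction of any bias can be computed from the document, and comparative bias requires exclusion that differs by arm. The only figure tied to the protocol's own inputs is the fall in nominal power from 80% to about 78–65% if an assumed 5–30% of patients are excluded, subject to the caveat about the formula. The sentence should be changed before the analysis.

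**What to change.** 1. Delete the exclusion sentence in Data analysis.
2. In Data analysis, Data monitoring and Suspension of clinical trials standards, state that a missed test or visit does not end MRI, adverse event or survival follow-up, and that all collected data are kept.
3. Replace the broken analysis-population sentence: every randomised patient is analysed in the assigned arm. Any analysis restricted to patients with complete attendance is secondary only.
4. For iPFS, censor patients without recorded progression at the last MRI. For overall survival, censor at the date last known alive. This replaces the rule that takes the last visit as death, a separate weakness that has to be settled once these patients are retained.
5. Use the planned multiple imputation for missing EDSS and quality of life values.
6. Add a sensitivity analysis for iPFS that counts loss to follow-up as progression, because attendance that differs by arm can still bias the main result.

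The cost is minor rewording, continued contact with patients who miss visits, and one extra analysis. No new visits, staff or committee are needed. The retained patients will have less complete records, and their censoring may be partly informative.

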### Sample size

It will be necessary to evaluate differences between the two groups; thus, the sample sizes of the experimental and control groups were set as n1 and n2, respectively. The two groups should have the same sample sizes; therefore, a single-sided test was used. The sample size calculation formula was:$${n}_1={n}_2=2{\left[\frac{\left({z}_{\alpha }+{z}_{\beta}\right)\sigma }{\delta}\right]}^2$$

where σ is the overall standard deviation (estimated to be 1.84); δ, the difference between the two sets of numerical variables (estimated to be 1); Zα, the standard normal value corresponding to the inspection level α; and Zβ, the standard normal value corresponding to β. If *σ* = 1.8 months, *δ* = 1 month, *α* = 0.05, *β* = 0.20, Zα/2 = Z0.05/2 = 1.96, and Zβ =Z0.20 = 0.842; then, by substituting the above formula, we obtain$${n}_1={n}_2=2{\left[\frac{\left(1.96+0.842\right)\times 1.8}{1}\right]}^2=50.9\approx 51$$

Hence, 51 cases will be included in the control group and 51 cases in the experimental group, with the total sample size being 102 cases.

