### Primary study outcome

#### Intracranial progression-free survival

The primary study outcome is iPFS, defined as the number of months from the start of TOMO or conventional 3D-CRT/IMRT to the occurrence of the first evidence of disease progression, which will be evaluated according to the Response Evaluation Criteria in Solid Tumors.

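### Propensity matching is prescribed for a 1:1 randomised comparison, where it either discards randomised patients or achieves nothing

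*Protocol article*

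**What the plan says.** Under Primary study outcome, the endpoint is a time to event: "The primary study outcome is iPFS, defined as the number of months from the start of TOMO or conventional 3D-CRT/IMRT" to first evidence of progression. Study settings and Study participants describe 1:1 randomisation with sequentially numbered, opaque, sealed envelopes.

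Under Data analysis, "iPFS and OS will be calculated using the Kaplan-Meier method", and a P value below 0.05 "will be considered significant in all statistical tests". The only test named is in the sentence "The chi-squared test will be used in combination with propensity matching analysis to minimize differences due to smoking, sex, weight loss". It adds geographic factors, economic status and education level, and gives its aim as avoiding baseline effects as far as possible. It does not say whether the matched analysis is primary or supportive.

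The Sample size section uses a comparison of two means with all 51 patients per arm analysed: "If *σ* = 1.8 months, *δ* = 1 month".

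**The concern.** Propensity matching is designed for non-randomised comparisons, where treatment choice depends on patient characteristics. Here allocation is random, so there is no such dependence to remove. What matching can do is change who is analysed. A caliper drops patients who have no close partner in the other arm. The remaining set is then no longer the randomised set, and its make-up depends on the propensity model, the caliper and the matching order.

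The choice of variables adds to the problem. Geographic factors, economic status and education level are on the list. KPS and number of metastases are not, although both are assessed under Inclusion criteria and would be more natural candidates for adjusting intracranial progression.

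At stake are the population behind the main comparison and the number of patients in it.

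**Working it through.** **1. The plan's own figure.** Inputs from Sample size: σ = 1.8 months, δ = 1 month, z-values 1.96 and 0.842.

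n per arm = 2 × [(1.96 + 0.842) × 1.8 / 1]² = 50.9, rounded up to 51.

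The stated 51 is reproduced. It uses the two-sided 1.96, although the text says "therefore, a single-sided test was used"; a one-sided 0.05 calculation would give 41. The section also gives an "overall standard deviation (estimated to be 1.84" value, which would need 54 per arm two-sided. Neither point affects what follows. The figure assumes that all 102 patients are analysed.

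**2. How many pairs survive matching.** The article gives no algorithm or caliper, so these are assumptions: 51 per arm, six covariates unrelated to arm (four binary, two with three levels), a logistic propensity model, greedy 1:1 nearest-neighbour matching and a caliper of 0.2 SD of the logit. Over 300 simulated trials the mean was 37.1 pairs (5th–95th percentile 32–42). About 14 of 51 patients per arm would be dropped although the arms differ only by chance. With no caliper and equal arms, all 51 pairs can be kept, and the two groups being compared are then the same as before matching.

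**3. Cost on the plan's own formula.** Power = Φ(δ / (σ√(2/n)) − 1.96), with σ = 1.8 and δ = 1.

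| n per arm | δ / (σ√(2/n)) | Power |
|---|---|---|
| 51 | 2.805 | 80% |
| 45 | 2.635 | 75% |
| 40 | 2.485 | 70% |
| 37 | 2.390 | 67% |
| 35 | 2.324 | 64% |

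This puts the loss of patients on the protocol's own scale. It is not the power of a time-to-event test.

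**4. Only if chi-squared were applied to progression by 2 years.** The article gives no hazard ratio or median. Assume exponential iPFS, complete 24-month follow-up, 51 per arm and HR 0.574. That HR is solved backwards as the effect giving a log-rank test 80% power with 102 events: exp(−2 × 2.802 / √102) = 0.574. Control probability of progression is p₀ = 1 − 0.5^(24/median); experimental is p₁ = 1 − 0.5^(24 × 0.574/median). Expected events are d = 51(p₀ + p₁). Log-rank power is Φ(|ln 0.574| √d / 2 − 1.96); chi-squared power is from the two-proportion formula.

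| Control median (months) | p₀ | p₁ | Log-rank | Chi-squared | Gap (points) |
|---|---|---|---|---|---|
| 4 | 0.984 | 0.908 | 78% | 40% | 38 |
| 5 | 0.964 | 0.852 | 76% | 50% | 26 |
| 6 | 0.938 | 0.796 | 74% | 56% | 19 |
| 8 | 0.875 | 0.697 | 70% | 59% | 11 |
| 10 | 0.811 | 0.615 | 66% | 59% | 7 |
| 12 | 0.750 | 0.549 | 62% | 57% | 5 |

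The log-rank test is ahead throughout, but the gap depends heavily on the assumed median.

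**5. The protocol's own hypothesis.** Background hypothesises an iPFS gain of about 5–8%. If iPFS is exponential, the HR is 1/1.05 = 0.95 to 1/1.08 = 0.93. Even with events in all 102 patients, log-rank power is Φ(ln(1.05) × √102 / 2 − 1.96) = 4% to Φ(ln(1.08) × √102 / 2 − 1.96) = 6%.

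**The case against.** The strongest objection is that a reader might infer that the arms' iPFS will be compared by a chi-squared test on progressed yes or no. The documents do not support that. iPFS and OS are assigned to Kaplan-Meier, and the chi-squared sentence gives its purpose as reducing baseline differences. A dichotomised iPFS appears nowhere. This stands, so step 4 describes one possible reading and not an established defect.

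Nor can the point rest on the absence of a log-rank or Cox analysis. The article is condensed, and a statistical analysis plan that is not shown may name one. That also stands. It does not remove the matching, which the article prescribes in terms; a plan that analysed all randomised patients unmatched would contradict it.

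Some further inferences go too far:

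- Matching does not undo allocation concealment, which protects assignment before treatment is known. What is lost is the randomised comparison at analysis.
- The matched set is not post hoc in the strict sense, because the matching and its variables are written down. Only the algorithm and caliper are open.
- Weight loss is a matching variable and also appears in an exclusion criterion. That criterion concerns advanced cancer with anaemia, weight loss or cachexia and gives no threshold, so lesser weight loss may vary among those enrolled. No contradiction is shown.
- KPS (above 80) and metastases (at most five) already have a restricted range, which weakens the complaint about their omission without removing it.

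Finally, the 37 pairs depend on an assumed caliper, and matching without one may lose nobody. In that case the procedure has no purpose.

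**Conclusion.** The concern holds for the propensity matching. In a trial randomised 1:1 it is not needed. Followed as written, it either drops randomised patients or leaves equal arms unchanged, and the variables chosen are not the best ones for adjustment. At an assumed 0.2 SD caliper about 37 of 51 pairs remain, and power on the protocol's formula falls from 80% to about 67%; the range is 75% to 64% for 45 down to 35 per arm. The direction is firm wherever a caliper is used; the size depends on the assumed caliper and covariates.

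For the chi-squared test the conclusion is conditional. If it were used for iPFS it would ignore event times and censoring and would lose about 5 to 38 points against the log-rank test, for assumed control medians of 12 down to 4 months at HR 0.574. The text does not clearly say that it will be so used.

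**What to change.** In Data analysis:

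- Delete the propensity matching.
- State that iPFS and OS are compared between all randomised patients, as assigned, by a two-sided log-rank test alongside the Kaplan-Meier curves, with a Cox hazard ratio and 95% CI.
- Handle baseline imbalance with one prespecified Cox model adjusted for a few variables already collected, for example KPS, number of metastases, sex and smoking.
- Limit the chi-squared test to categorical items such as response or adverse event rates.

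The statement in the same section that patients who miss assessments are left out of the final efficacy analysis would have to be brought into line with analysing everyone randomised.

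The cost is protocol and analysis-plan wording. No new data or visits are needed, and SPSS, already named, runs both analyses. The change should be made before outcome data are analysed. It keeps the patients the trial has randomised but does not make the trial adequately powered for a 5–8% gain; that is a separate matter.

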## Dissemination

### Data monitoring

The Data Monitoring Committee (DMC) is composed of all the authors, with [name] as the team leader, responsible for testing the accuracy and authenticity of data and reviewing whether the operation of obtaining data is standardized. If the patient fails to complete the relevant examination, evaluation, or follow-up within the agreed time or cannot suspend the study, part of the clinical trial of the patient will be suspended.

